## Abstract

**Background:**

Extreme heat events are intensifying worldwide due to climate change, posing significant health risks and economic challenges. The urban heat island effect poses extra challenges to the inhabitants of cities, especially in the global South.

**Methods:**

This trial aims to evaluate the effectiveness of a comprehensive resilience and heat adaptation bundle (ReHAB) that integrates behavioural and structural interventions to reduce heat-related morbidity and mortality and improve internal ambient conditions in urban settings of Pakistan. This would be a cluster randomised controlled trial where 22 clusters comprising approximately 70–80 households per cluster will be randomly assigned to intervention and control arms in a 1:1 ratio. The intervention ReHAB is a combination of community education and awareness and targeted structural modifications, including reflective paints, shading, sustained energy/power, improved ventilation, and community shaded spaces. Data on health and behaviours will be collected via wearable devices and household surveys and environmental sensors will be used to capture indoor and outdoor thermal conditions.

**Expected outcomes:**

The findings from this trial will provide evidence for the effectiveness of the ReHAB bundle on indoor ambient environments and health and help policy recommendations for urban areas, especially for the global south.

**Ethics and dissemination:**

The study has received ethical approval from the Aga Khan University (AKU) (Ref: 2025-11548-35626) and the Pakistan National Bioethics Committee (Ref: 4–87/NBCR-1065/23/1736). Written informed consent will be obtained from all participants before enrolment. Referral pathways to healthcare facilities will be established to ensure timely management of complications. Findings will be disseminated through peer-reviewed publications, scientific conferences and engagement with policymakers and public health stakeholders. Results will also be shared with participants and communities through meetings and informal sessions to raise awareness and support evidence-based heat adaptation.

**Trial registration number:**

NCT06991543.

STRENGTHS AND LIMITATIONS OF THIS STUDYUse of weather stations, environmental devices, personal wearable devices and other data collection measures will enable triangulation of household environment, individual exposures, health outcomes and physiological profiling.Blinding of participants and field teams is not feasible because of the nature of the structural and behavioural interventions.We anticipate challenges in compliance with wearable devices and device discomfort during hot weather.

## Background

 Anthropogenic climate change, defined as long-term shifts in temperatures and weather patterns, has significantly raised global average temperatures and extreme weather events, particularly heatwaves, have increased in frequency and intensity in regions of South Asia, West Africa, the Middle East and North Africa.^1
2^ Approximately 40% of the global population resides in regions where annual temperatures exceed 30 °C^3^ and deadly heatwaves in India and Pakistan are approximately 30 times more likely due to climate change.^4^

Extreme heat enhances the risk of morbidity and mortality, particularly among the most vulnerable,^5–10^ and between the years 2000 and 2019, heat-related deaths have averaged 489 000 annually, with Asia and Europe accounting for 45% and 36% of these fatalities, respectively.^4
11^ Beyond its direct health effects, extreme heat undermines daily work and the quality of life by limiting outdoor work and social activities and exacerbating stress which poses serious risks to mental health and psychosocial well-being.^12
13^

In the major cities of Pakistan, rapid urbanisation and expansion of informal settlements have led to the rise in dense concrete construction and loss of green spaces, with compounding strain on water and energy supplies further exacerbating heat stress,^14^ known as the urban heat island (UHI) effect.^15–19^ Satellite-derived land surface temperature data from 2001 to 2022 shows that the densely built-up areas of the cities of Lahore, Karachi and Faisalabad in Pakistan can experience elevated temperature differences of up to 4 °C during the day, with even greater differences at night when compared with its peripheral.^20^ In addition, low-income urban settlements are not homogeneous and often comprise a mix of housing typologies, including reinforced concrete (RCC) structures, semi-permanent dwellings and in some cases, mud-brick housing. Variations in building materials, ventilation and housing density can substantially influence indoor heat exposure and vulnerability to extreme heat. There has also been a major architectural shift, where modern concrete structures have replaced traditional designs. Colonial-era houses were oriented to face the sea breeze, featured high ceilings, deep verandas (‘baraamdahs’) and aligned window openings that encouraged through-drafts.^21–23^

A scoping review found that most adaptation research comes from the Global North, limiting evidence from Low and Middle Income Countries (LMICs).^24^ In June 2015, Karachi experienced a catastrophic heatwave that resulted in over 1200 deaths in a day, disproportionately impacting low-income populations, thus exposing vulnerabilities of the urban infrastructure and health systems.^25^ This led to the formulation of the ‘Karachi Heatwave Management Plan’ in 2017 which comprised early warning systems and emergency coordination mechanisms.^26^ Despite these advances, the long-term community-level resilience remains neglected, a randomised controlled trial by Razzak *et al* demonstrated that community-based education can significantly improve heat literacy and modestly reduce heat-related health events in low-income areas^27^ and similarly, the Ahmedabad Heat Action Plan in India has shown a reduction in heat-related mortality through early warnings, public awareness campaigns and cooling centres.^28^

Most strategies remain fragmented with a focus on early warnings or public messaging and rarely focus on integrating structural solutions that can address the physical determinants of heat exposure, especially in informal urban settlements. There is emerging evidence on the effectiveness of improved vegetation, reflective paints, cool pavements, heat education and early warning systems which have been tested in limited settings.^27^ The Structural Heat Adaptation and Education in Urban Settings trial is therefore timely and essential and represents one of the first rigorously designed, cluster-randomised evaluations of a comprehensive community-based heat adaptation package that integrates behavioural, structural and community-led components.

## Methodology

### Objective

#### Primary

To assess the feasibility and effectiveness of a resilience and heat adaptation bundle (ReHAB) on heat-related health risks for vulnerable populations in urban settings of Pakistan.To assess the effectiveness of ReHAB on the quality of life of vulnerable populations in urban settings of Pakistan.

#### Secondary

To evaluate the effectiveness of ReHAB on indoor heat in urban settings.To evaluate the impact of ReHAB on key physiological variables (sleep quality, heart rate, physical activity and energy expenditure) in adults residing in urban settings.

### Study setting

Karachi has a tropical semi-arid climate where summers are sweltering, humid and evenings are breezy, while winters are brief, pleasant and arid, with clear skies most of the year and daily average temperatures ranging from 13°C to 34°C.^28^ In recent years, the temperature has regularly touched 40 °C and above for days and in June 2024, Karachi experienced the hottest day of the year, with temperatures reaching 47.2°C.^28^ This study will be conducted in representative urban settlements in Karachi (Bilal Colony and Mehran Town), which primarily comprises mixed construction typologies as most buildings are RCC structures or girder and concrete tiles with load-bearing block masonry walls, while some lower-income strata have semi-permanent constructions using concrete blocks, mud bricks or corrugated metal sheets.

### Study design

This study is a 2-year prospective, cluster randomised controlled trial designed to evaluate the effectiveness of ReHAB intervention in urban, low-income settings. Clusters are defined as localities comprising 70–80 households which typically span one to two contiguous streets, and these clusters will be randomly assigned to either the intervention or control arm in a 1:1 ratio (figure 1). Due to the nature of the intervention, blinding of participants and researchers will not be feasible, but data analysis would be blinded. The trial is registered on clinicaltrial.gov with trial registration number NCT06991543. The study is planned to start from 1 January 2026 to 31 December 2027.

**Figure 1 F1:**
[figure not shown]
Study design diagram.

### Population

The population of this trial will include all members of the households within the selected clusters who provide informed consent. A subset of eligible adults aged 18–60 years will be randomly selected for detailed physiological and personal heat exposure assessments.

#### Exclusion criteria

We will exclude any clusters that present significant accessibility or security concerns, have inadequate structural stability for retrofitting or have limited community cooperation. For the subset population, individuals unwilling to wear both (Fitbit and temp-u) devices simultaneously, individuals with cognitive or severe mental health conditions that may impair their ability to provide informed consent or comply with study procedures and individuals with severe physical disabilities that would limit participation in physiological monitoring will be excluded.

### Outcomes

All primary, secondary, and outcomes assessed for the subset of the population, along with definitions, are provided in table 1 and figure 2.

**Table 1 T1:** Outcome and definitions

Primary outcomes	
Heat-related illness	Defined as a documented heat condition/illness according to the International Classification of Disease (ICD-11) and institutional classification, which classifies heat-related illness as heat stroke, heat syncope, heat exhaustion, heat fatigue, heat cramps and heat rash ^37 38^(figure 2).
Quality of life	Defined as an individual’s perceived quality of life within the context of their culture, value systems, personal goals, expectations, standards and concerns.
**Secondary outcomes**	
Health outcomes	
All-cause mortality	Defined as the total number of deaths in the study population over the study period
Hospital visit/ hospitalisation	Defined as the number of hospital admissions (primary, secondary or tertiary facilities) during summers
Environmental outcomes	
Heat index	Indoor heat index (temperature and humidity) (^39^)
Universal Thermal Climate Index (UTCI)	Defined as a biometeorological index that describes the human body’s physiological response to the environment. It integrates air temperature, humidity, wind speed and radiant temperature to assess the overall thermal stress on the human body
Thermal comfort	Defined as change in the condition of mind that expresses satisfaction with the thermal environment
Outcomes measured for subset of population (Individual Level)	
Personalised heat exposure	Defined as mean daily external temperature each individual experiences (indoors and outdoors).
Heart rate	Defined as mean heart rate measurements (beats per minute) taken at 1-hour interval.
Sleep quality	Defined as a biological process that alternates between non-rapid eye movement (NREM) sleep and rapid eye movement (REM) sleep.
Physical activity	Defined as mean daily duration of sedentary, lightly active, moderately active and very active.
Energy expenditure	Defined as the average total number of calories burnt in a day.
Economic outcomes	
Cost effectiveness	Defined as the difference in cost divided by the difference in health effect between the intervention and control groups

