##### Sessions

The community sessions will be led by CGs and held separately for males and females. It will consist of:

CG meetings (triggering session).Meetings supervised by research staff.

The sessions will focus on educating the community. The meeting schedule will be as follows:

Summer (April–June):Fortnightly community meetings.Weekly WhatsApp video messages.Weekly weather alerts.Late Summer (July–October)Monthly community meetings.Weekly WhatsApp video messages.Weekly weather alerts.Winter (November–March):Community meetings every other month.No WhatsApp video messages.

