### Data collection from subset population

Monthly data will be collected for in-depth understanding of heat stress and intervention effectiveness within the subset population (table 3). This will include thermal comfort, mental health and heat exposure assessment.

**Table 3 T3:** Schedule of outcome assessments and follow-up activities

Parameter	Time points	Details	Devices/Tools	Population/Unit
Primary outcomes				
All heat-related illness	Weekly during peak summers	Heat-related illnesses	Weekly community survey, health facility data, community surveillance	All members of included households
Quality of life	Mid of April, July and December for two consecutive years	Quality of life mean score	WHOQOL-BREF* questionnaire	Indexed adults of all included households
Secondary outcomes				
All-cause mortality	Weekly during peak summers	Any mortality occurring within the included clusters	Weekly community survey, health facility data, community surveillance	All members of included households
Hospital visit/hospitalisation	Weekly during peak summers	Any hospital admission or hospital visit occurring within the included clusters	Weekly community survey, health facility data, community surveillance	All members of included households
Indoor heat index	Continuous throughout the year	Indoor data loggers	iButton, Kestrel Drop D2, Temp-U	All included households
Thermal comfort (home)	Monthly	Self-reported comfort levels	Thermal comfort survey adapted from CHEQ-5†	Indexed adults randomised for sub-group
UTCI§	Continuous throughout summers	Outdoor only	Kestrel Drop D2, Kestrel 5400, HOBO weather station	Overall catchment area
Outcomes measured for subset of population				
Personalised heat exposure	Baseline, monthly	Occupation, sun exposure, illness history, daily routine	Structured survey tool (adapted from HotHaps)‡ and Temp-U	Indexed adults randomised for sub-group
Physiological strain markers	Continuous throughout summers	Heart rate, sleep cycles, VO₂¶ max	Fitbit Inspire 3	Indexed adults randomised for sub-group

* WHOQOL-BREF: World Health Organization Quality of Life - Brief

† Cold and Heat Exposure Questionnaire

‡ High Occupational Temperature Health and Productivity Suppression

§ Universal Thermal Climate Index

¶ Volume of Oxygen

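### All-cause mortality is defined over the whole two-year study period, but its collection is scheduled only in peak summer

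*Protocol article*

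**What the plan says.** Protocol article, Table 1 (Outcomes), all-cause mortality: "Defined as the total number of deaths in the study population over the study period". Study design fixes that period: "The study is planned to start from 1 January 2026 to 31 December 2027".

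Protocol article, Table 3 (under Data collection from subset population), all-cause mortality row: the time point is "Weekly during peak summers" and the detail is "Any mortality occurring within the included clusters". The sources are a weekly survey in the community, health facility data and community surveillance. The unit column names the members of included households.

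The next outcome in both tables is a useful comparison. Hospital visits have the same Table 3 time point as mortality, but their Table 1 definition carries the matching limit: "Defined as the number of hospital admissions (primary, secondary or tertiary facilities) during summers".

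Secondary outcome analysis allows mixed-effects Poisson or logistic models for mortality, or a Cox model where individual times are available. Results are to be reported as ratio measures. No at-risk window is given for mortality.

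**The concern.** The definition and the collection schedule of one outcome name different time windows. A team that follows Table 3 will hold a summer count of deaths; a team that follows Table 1 will report a two-year count. Unless the two are reconciled beforehand, the choice of window falls to whoever prepares the analysis, possibly after the data are seen.

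The window also changes the meaning of the result. For a heat intervention, the effect on deaths in the hot months and the effect on deaths over the whole calendar are different quantities. Deaths are also rare, so leaving part of the period unobserved removes events that the comparison can ill afford to lose.

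**Working it through.** The article states no expected number of deaths, death rate or power for mortality, so there is no figure to reproduce. The check compares the two windows and then searches for any statement that would close the gap.

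**Step 1. Defined window.** From Study design, 1 January 2026 to 31 December 2027: 365 + 365 = 730 days, or 24 months.

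**Step 2. Scheduled window.** The article gives no dates for peak summer. The nearest labels are in the meeting schedule under Sessions, where summer is April to June ("Summer (April–June):Fortnightly community meetings") and late summer is July to October. Using these as proxies, which is an assumption:

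- April to June: 3 months × 2 years = 6; 6/24 = 25%. In days, 91 × 2 = 182; 182/730 = 24.9%.
- April to October: 7 months × 2 years = 14; 14/24 = 58%. In days, 214 × 2 = 428; 428/730 = 58.6%.
- A narrower reading, May and June only: 61 × 2 = 122 days; 122/730 = 16.7%.

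On the first two readings, 75% to 42% of the defined period has no scheduled collection of deaths.

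**Step 3. Does another part of the article close the gap?**

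- Household data collection describes baseline, monthly or weekly follow-up and endline surveys. Death is not among the variables named, nor is it in the Box 1 section titles.
- The same section says that several sources are used so that events are not missed during the study, but the sentence concerns signs and symptoms of heat-related illness.
- Table 3 marks the indoor heat index for year-round recording, so the table does state year-round collection where it is intended.
- The hospital outcome is limited to summers in both tables. The limit was written into one definition and not the other.

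No statement closes the gap.

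**Step 4. Effect on the count.** If deaths were spread evenly over the year and none from the off-season were recovered, the share of the defined deaths outside scheduled collection would equal the share of uncovered time: 42% to 75%. More deaths in the hot months, or recovery at later visits, would make it smaller.

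**Step 5. Effect on the rate ratio.** Let each arm have D deaths over person-time T, and let the schedule capture the same fraction f of deaths in both. Then (f·D1/T1)/(f·D0/T0) = (D1/T1)/(D0/T0), so a common f cancels. This needs an effect that is constant over the year. If the effect differs by season, then with equal person-time between arms the two-year ratio is w·RR(summer) + (1 − w)·RR(off-season), where w is the share of control-arm deaths that fall in summer. The summer-only ratio is RR(summer) alone. That is a difference of estimand rather than a bias.

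**The case against.** **Death is permanent and can be dated later.** A winter death can be learned of at the next household contact. Table 3 places quality-of-life visits in mid-April, July and December of both years with an index adult of every included household, and there is an endline survey. The list of survey variables is not presented as exhaustive, and the questionnaire is not shown. This stands: a reader might infer that off-season deaths are necessarily lost and the defined count cannot be produced, but the documents do not show that. They show only that no such collection is stated. Nor can it be said that most deaths would be missed, since under the April to October reading 58% of the period is covered.

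**No wrong denominator is stated.** A reader might infer that mortality rates will be understated by a factor of 24/14 = 1.7 to 24/6 = 4, by dividing summer deaths by two-year person-time. The article never sets that denominator. The only one it gives, for heat-related illness under Primary outcome analysis, is person-weeks at risk. Even if the error were made, it would affect absolute rates and largely cancel in the planned ratio measures.

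**The population wording is a small matter.** The Table 3 detail refers to deaths within the clusters, but the unit column of the same row limits it to members of included households. One phrase needs tidying; it is not a separate contradiction.

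**A summer-only target is defensible.** For a heat intervention, off-season deaths may dilute the effect. This also stands, and it is why restricting the definition is as acceptable a repair as extending the collection.

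None of this removes the conflict between the two tables.

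**Conclusion.** The point holds as an internal contradiction: the outcome defined in Table 1 is not the outcome that the Table 3 schedule delivers. Scheduled collection covers about 25% of the defined period if peak summer is April to June, and about 58% if it is April to October. Both figures rest on borrowed season labels, because peak summer is undated. The consequences are fewer events and an estimand other than the one defined. The size of any under-count cannot be fixed from the article, since later recovery is neither stated nor excluded.

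A schedule shared by both arms does not in itself bias the comparison. One caution applies: Table 3 lists community surveillance as a source, and the article describes community groups, which carry out surveillance, only in the intervention clusters. Informal recovery of off-season deaths could therefore differ by arm. This is an inference, but it is a reason for one explicit rule applied equally.

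Mortality is a secondary outcome with no stated power calculation. The sample size, the primary analyses and the fixed-sequence test are unaffected. The correction should still be made, because the text is wrong as written and cheap to repair.

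**What to change.** Make Tables 1 and 3 agree in one of two ways.

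- **(a) Keep the study-period definition.** Add a household-roster question on deaths, with date of death, to the April, July and December visits and to the endline survey, worded and asked identically in both arms. List these contacts in the Table 3 mortality row. State that the outcome closes at the last contact at which the question is asked, since the final December visit falls before 31 December 2027.
- **(b) Restrict the definition.** Reword Table 1 to deaths during the summer surveillance windows, as is already done for hospital admissions, and give those windows calendar dates.

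In either case, state under Secondary outcome analysis that at-risk time in the Poisson or Cox model matches the chosen window. Under (b), a person who dies between the two summers must leave the risk set before the second, so a roster update at the start of that summer is still needed. Replace the reference to deaths within clusters by deaths among members of included households, in both tables.

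The cost of (a) is one question at contacts already scheduled. The cost of (b) is a change of wording, a set of dates and the roster update. Neither changes the sample size.

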#### Community education and awareness

This component of the ReHAB will involve community mobilisation, which will include education and awareness activities throughout the intervention duration. Community groups (CGs) will be established in all the 11 intervention clusters with separate male and female representatives working as volunteers. The CGs will be responsible for community mobilisation activities and surveillance for the primary outcome (heat illness). Each CG will comprise 6–8 members, representing a diverse group of people, including local government members, local elders, religious leaders and prominent male and female members of the community. These CGs will facilitate dissemination of early warnings regarding heat waves, awareness sessions and door-to-door outreach focused on heat-health fundamentals, hydration practices, appropriate clothing and daily activity scheduling. CGs will also maintain simple logbooks to track any visit to a healthcare facility within their catchment area.

Also building on this CG platform, hands-on demonstration and reinforcement of specific cooling behaviours will be emphasised. CG members, along with the study team, will lead small-group demos on practical techniques, such as setting up shade cloths, using light-coloured clothing, wet-towel wraps, misting fans, changing work timings and following work-rest-shade cycles to reduce heat exposure. CGs will also distribute the relevant information, education and communication (IEC) material. This structured, behaviour-focused delivery aims to ensure both the uptake and sustainability of protective cooling practices. Community hydration arrangements, like setting up temporary drinking water facilities (‘Sabeels’), will also be put in place as part of the intervention package to reduce dehydration among outdoor workers.

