#### Secondary outcome analysis

Secondary outcomes will be analysed within the same cluster randomised framework, accounting for clustering at the design level using mixed-effects models or generalised estimating equations as appropriate to the distribution of each outcome. All-cause mortality and hospital visits/hospitalisations, measured as counts or rare events, will be analysed using mixed-effects Poisson or logistic models (or Cox proportional hazards models where individual-level time-to-event data are available), with results reported as IRRs, risk ratios or HRs with 95% CIs. Indoor heat index and UTCI, both continuous environmental exposure measures, will be assessed using linear mixed-effects models with random intercepts for clusters and adjustment for temporal variation to estimate mean differences between trial arms. Thermal comfort, measured either as a continuous score or ordinal response, will be analysed using linear mixed models or ordinal logistic mixed-effects models depending on scale properties. Subgroup analyses will be conducted by including interaction terms between intervention assignment and key effect modifiers such as age (WRA, children and elderly), sex and occupational exposure. All models will be adjusted for relevant covariates where appropriate, and robustness will be assessed through sensitivity analyses including alternative correlation structures. Cost-effectiveness analysis will be conducted to evaluate the economic feasibility of different adaptation strategies.

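### The hospital outcome has two definitions and two time windows, and one of its listed event sources is described for the intervention arm only

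*Protocol article*

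**What the plan says.** The Outcomes section of the protocol article refers the reader to Table 1 for definitions. The row for hospital visit/hospitalisation in that table reads "Defined as the number of hospital admissions (primary, secondary or tertiary facilities) during summers". The label therefore covers visits and the definition does not.

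Table 3, the schedule of assessments, carries the same row label. It describes the event as "Any hospital admission or hospital visit occurring within the included clusters" and sets the timing as "Weekly during peak summers". It gives three sources: a weekly community survey, health facility data and community surveillance.

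The secondary outcome analysis section treats "All-cause mortality and hospital visits/hospitalisations, measured as counts or rare events", to be analysed with Poisson, logistic or Cox models. It does not say whether admissions, visits or both make up the count.

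On surveillance, the community education section says "Community groups (CGs) will be established in all the 11 intervention clusters" and "CGs will also maintain simple logbooks to track any visit to a healthcare facility within their catchment area". The training section adds that these groups will build a network to pick up heat illness and hospital visits. The control arm section provides for nothing beyond routine care and existing government information.

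**The concern.** An admission and a facility visit are different events. An admission marks illness severe enough for inpatient care. A visit also depends on how readily people seek care. A count of one is not a substitute for a count of the other, and a count of both is a third quantity. With the definition open, the same data could yield different rate ratios, and the choice could be made after the data are known.

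The second issue is capture. If one listed source operates in the intervention clusters only, events that no other source finds enter the intervention numerator and have no counterpart in the control numerator. That pushes the rate ratio upwards, against the intervention, whatever the true effect.

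**Working it through.** **No planned figure to reproduce.** The Sample size section covers heat-related illness, quality of life and heart rate in the sub-sample. It gives no rate, effect or power for the hospital outcome, so the check is mainly a comparison of texts.

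**Numerator and window.**

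| Place | Events | Window |
|---|---|---|
| Table 1, row label | visits and hospitalisations | none |
| Table 1, definition | admissions only | summers |
| Table 3 | admissions or visits | weekly in peak summers |
| Secondary outcome analysis | both named, count not specified | none |

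The Table 3 event set contains the Table 1 set and is wider. The Table 3 window, read literally, is narrower. No other text reconciles them.

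**Source by arm.**

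- Weekly survey: the household data collection section places follow-up surveys in all 22 clusters, so it covers both arms.
- Facility records: reported visits are verified where feasible. Verification acts on visits already reported. Table 3 also lists facility data as a source, without describing a separate search of records.
- Community surveillance: the groups and their logbooks are described for the 11 intervention clusters only.

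Let c be the events known only through community groups, as a fraction of the intervention-arm events found by the other sources. Then observed IRR = true IRR × (1 + c). If the weekly survey finds everything, c = 0 and there is no bias. At an assumed c of 0.10, a true IRR of 1.00 is observed as 1.10, and a true 0.70 as 0.70 × 1.10 = 0.77. The formula applies to admissions and visits alike.

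**Why the effect of the definition cannot be sized.** Let r be visits per admission in the control arm. The IRR for the combined count is (IRR for admissions + r × IRR for visits)/(1 + r). All inputs below are assumed. The IRR for admissions is fixed at 0.70.

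| IRR for visits | r = 5 | r = 10 | r = 20 |
|---|---|---|---|
| 0.70 | 0.70 | 0.70 | 0.70 |
| 1.00 | 5.7/6 = 0.95 | 10.7/11 = 0.97 | 20.7/21 = 0.99 |
| 1.10 | 6.2/6 = 1.03 | 11.7/11 = 1.06 | 22.7/21 = 1.08 |

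Visits make up r/(1 + r) of the combined control-arm count: 5/6 = 83% at r = 5 and 20/21 = 95% at r = 20. The definition makes no difference if both events respond equally. It hides most of an admissions effect if visits do not change. The combined ratio passes 1 only if visits rise. With a 10% rise this needs 0.7 + 1.1r > 1 + r, that is, r above 3. The article supplies neither r nor either ratio, so no cell is an estimate.

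**The case against.** The strongest reply is that Table 1 defines outcomes while Table 3 schedules data collection. Collecting both events is compatible with either definition, and the defect may be one loosely worded cell. That is a likely account of how it arose. It does not settle the count, because the label in Table 1 itself includes visits and the analysis section repeats both terms. The article does define the outcome, so this is a conflict in its text and not a detail left to a fuller document.

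It can also be said that the outcome is secondary, lies outside the fixed-sequence test, and that data analysis is to be blinded. All true. Blinding tempers the worry about a later choice of definition without removing it. The weekly household visits similarly limit the capture problem, and may leave it small.

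Four stronger readings are tempting, and the document supports none of them:

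- A reader might infer that visits and admissions will be pooled into one count. The analysis section names them together but does not say so.
- A reader might infer that education will raise visits while lowering admissions. The listed content is "door-to-door outreach focused on heat-health fundamentals, hydration practices, appropriate clothing and daily activity scheduling", which does not name care-seeking. The abstract's statement "Referral pathways to healthcare facilities will be established to ensure timely management of complications" is not tied to one arm. Opposite movement is only a possibility.
- A reader might take a combined ratio above 1 as the expected result. It rests wholly on assumed inputs.
- A reader might think the logbooks affect visits alone. Table 3 gives community surveillance as a source for the whole row, so admissions are exposed too.

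**Conclusion.** The concern holds as an internal inconsistency with a related problem of capture. Two numerators and two windows are open for one secondary outcome. One listed source of events is described for a single arm, so events known only through it would tilt the comparison against the intervention.

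The size of either effect cannot be stated from the document. The effect of the definition depends on the unknown ratio of visits to admissions and on how each responds. The capture bias depends on how many events only the community groups would find, which could be none. The capture point also assumes that no equivalent surveillance runs in control clusters; the article describes none. The sample size and the tests of the two co-primary outcomes do not depend on this outcome. It should be corrected because the result would otherwise be hard to interpret and the correction is nearly free.

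**What to change.** Use one definition and one window in Table 1, Table 3 and the secondary outcome analysis section. Count and report admissions and visits separately, each under its own label, and state in the analysis section which count each model uses.

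For the between-arm analysis, count only events found by the weekly household survey run in both arms, and apply facility-record verification in the same way in both. An event that a community group logged still counts if the weekly survey also finds it. Keep reports known only to community groups for a sensitivity analysis.

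The cost is revised wording in two tables and the analysis section. The source of each report and the type of event must also be recorded so that the counts can be separated. The downside is that slightly fewer events enter the main comparison.
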